## Abstract

**Background:**

Falling is a major trauma that can occur with aging, leading to very significant psychological and physical health effects with financial and societal consequences. It is therefore essential to explore therapeutic treatments that can reduce this risk. Some recognized effective treatments exist, concerning in particular the re-education of the muscles of the lower limbs. However, to our knowledge, none of them focus on the cervical spine although the latter is located at an essential physiological crossroads. Manual therapy, which has already demonstrated its impact on pain and balance parameters in the elderly, could be a painless and non-invasive tool of choice in addressing this problem.

**Methods:**

Interventional study (not related to a health product), monocentric, prospective, controlled, randomized double-blind (patient and evaluator performing the measurements). The experiment will take place over three measurement periods on D0, D7 and D21. On D0 subjects will be randomized in 2 groups: experimental and placebo group. Both groups will be assessed on: Short Physical Performance Battery test score, walking speed, lower limb strength, balance, heart rate variability and cervical spine strength and mobility. Then the experimental group will receive a myofascial release protocol applied to the cervical spine and the placebo group will receive a placebo light touch protocol. The intervention will be followed by the same measurements as before. This schedule will be reproduced on D7. On D21, only one assessment will be done.

**Discussion:**

This study started in 2020 but could not go beyond the inclusion phase due to the COVID pandemic. It is envisaged that recruitment could resume during 2022.

*Trial registration*: Registered by the Comité de Protection des Personnes—Sud Méditerranée; under the title “Prévention des troubles de l’équilibre chez le senior: influence de la thérapie manuelle appliquée au rachis sur les paramètres statiques et dynamiques», n° 19.12.27.47.259 in date of February 4, 2020.

Registered by ClinicalTrials.gov ID: NCT05475652; under the title « The Influence of Manual Therapy Applied to the Cervical Spine in the Prevention of Balance Disorders in the Elderly (ManEq)”.

## Background

Falls represent a major health problem in elderly subjects because of their high prevalence and the seriousness of their physical, functional, psychological and financial consequences. Indeed, about 30% of independent people living in the community over 65 years old and 50% of those over 80 years old suffer at least one fall per year; a third of the fallers experience repeated falls [1]. The human and economic cost of falls increases along with the aging of the population, particularly in Western societies. In 2015, EuroSafe (European Association for Injury Prevention and Safety Promotion) [2] classified falls as the 3rd most common cause of disability among the elderly and one of the main causes of admission to specialized institutions.

Prevention of falls is widely recognized as one of the priorities for healthy and active aging of the population. Most recommendations for fall prevention, such as STEADI [3] or The ProFouND [4], call for regular assessments of elderly patients at risk and the provision of appropriate interventions. Van Voast Moncada et al. [5] summarized the different interventions evaluated in the literature, such as therapeutic education, dietary supplementation, functional rehabilitation to improve walking, strength or balance, treatment of hypotension, review of medication, podiatry or even management of vision problems or home design. Taken separately, each intervention has only a moderate impact on the risk of falling, and elderly people at risk of falling should be offered a broader protocol combining different methods [6]. Prevention of physical deconditioning is a prerequisite for "successful aging" [7]. Various elements have been identified as physical components [8] that contribute to the maintenance of autonomy and can therefore be used as a control during management. In elderly people who fall, there is a maladaptation of the balance strategy: weakened postural and general control, impaired visual feedback, as well as impaired proprioceptive and vestibular systems and neuromuscular coordination [9, 10]. The loss of lower limb strength directly influences Walking Speed (WS) [11], which is a recognized marker for predicting the risk of falling and is correlated to static and dynamic balance [12]. Age leads to the appearance of a cautious attitude with a reduction in WS [13] and a change in the distribution of support on the ground with an increase in pressure peaks at the level of the hindfoot and a decrease in support at the level of the hallux [14–16].

Spinal curvatures change with age, tending to a general increase in curvatures, an increase in asymmetries and an protraction of the head [17, 18] which may influence balance in the senior citizen. The neurological system also undergoes major modifications with a reorganization of the motor units [19], a decrease in the number of mechanoreceptors, and an alteration of the function and vestibulospinal reflexes [20]. Finally, the aging of the autonomic nervous system and more particularly of its parasympathetic component [21] may indirectly influence balance through its link with the cardiovascular system [22]. This is why the analysis of Heart Rate Variability (HRV) is a good indicator in the evaluation of the risk of falling due to orthostatic decrease in the elderly [23].

From a clinical point of view, the cervical spine could be of particular importance due to its position and constitution: at crossroads of articular, visual and vestibular proprioceptive afferents, rich in neurological and motor elements [24–26]. Its role is mechanical (shock absorption of movements [27] and stabilization of vision [28]); but also neurological (regulation of the autonomic nervous system). Quek et al. [29], have shown that a decrease in cervical mobility and the presence of rotational asymmetry caused an alteration in anteroposterior oscillations during static equilibrium. They hypothesize that in subjects unable to effectively recruit the muscular and proprioceptive system of the neck, a compensatory system based on vision and vestibular system comes into play. This suggest that preserving cervical movement capacity across lifespan could limit compensations and risk of falling. The role of the tone of the cervical musculature seems to be essential since it has been shown [30] in young subjects that muscular fatigue in that area reduces the speed of displacement of the Center of Pressure (CoP), and in elderly subjects there is a modification of the recruitment pattern of the neck muscles in favour of the superficial muscles (to the detriment of the deep muscles) which favours the modification of the cranio-cervical angle and the orientation of the lordosis, generating an protraction of the head [31].

If the management of the cervical spine seems to be of interest in balance strategy, its vascular and neurological environment makes investigation and local treatment delicate especially in elderly. Myofascial Release (MFR), which is a form of manual therapy, seems particularly appropriate as it is non-invasive and can be adjusted to the recommendations of use. MFR needs application of a low load, long duration stretch to the myofascial complex, intended to restore optimal length, decrease pain, module neural transmission and improve function. The effects of neuromuscular stimulation of the cervical region remain poorly explored. Studies have shown that the application of vibrations to the cervical spine improves sensorimotor function and decreases postural sway in subjects with neck pain, while it alters head positioning in healthy subjects [32, 33]. Applied on C4 level this technique could provide stimulation of the carotid sinus and its baroreceptors, the superior cervical ganglion, the nuchal ligament, the longus neck muscle and the vestibulospinal reflex. An other technique commonly applied in MFR, usually called “suboccipital decompression”, seems to have an interesting impact on different postural determinants, in particular the cranio-cervical angle, the position of the head or even the stiffness of the posterior chains of the lower limbs [34, 35]. This technique enables an action on the oculo-cephalogyre muscles (the rectus capitis posterior major and minor, obliquus capitis superior and inferior) and the vestibulospinal reflex as well as the upper cervical proprioceptors, the neurovegetative structures of the posterior torn hole (X and XI) and of the carotid corpuscle by anastomosis. Other manual protocols aimed at the myofascial system as a whole or more specifically in the neck region have been evaluated and seem to indicate a favourable effect on balance, especially on anteroposterior sway [36] which is a parameter characterizing the displacement of the CoP, cervical mobility [37, 38] or even the Time Up and Go Test (TUGT). Unfortunately, these studies are sometimes of questionable methodological quality whether this is because of a small number of subjects, the absence of a controlled or placebo group or even a timing of different treatments depending on the groups.

However, there is no consensus on the frequency or number of treatments necessary with MFR, regardless of the reason for which they are used, for example: chronic low back pain, fibromyalgia, functional capacities… [39, 40]. Whatever the modality of application (massage or osteopathic manual therapy) or location (lower limb or trunk) it seems that only one MFR session have a limited or even non-existent effect on balance [41, 42] while recent studies have shown that two sessions can [43, 44].

To our knowledge, no study has yet proposed to evaluate the effect of a cervical spine MFR protocol on balance in older adults. The main hypothesis of the present study is that a two sessions MFR protocol have a beneficial impact on the balance and motor performance of older adults, which will result in improved balance and WS in the experimental group compared to the placebo group. The study also aims to propose an assessment of the physical parameters of balance, looking for links to validate the contribution of the cervical spine in compensatory mechanisms.

### Primary and secondary objectives

The primary objective of this work will be to evaluate the influence of some MFR techniques address to cervical spine on WS and SPPB (Short Physical Performance Battery test) score. It can be assessed by the main hypothesis:

H0: SPPB score and WS of MFR protocol group ≤ SPPB score and WS of light touch group.

H1: SPPB score and WS of MFR protocol group > SPPB score and WS of light touch group.

Secondary objectives will be to evaluate the influence of the protocol on other measured balance parameters, including cervical strength and mobility as well as lower limb strength, ground support and HRV. The data can also be used to explore the relationships between the different parameters.

## Methods

### Design

A two-armed (sham group and intervention group) randomized controlled trial designed according to the SPIRIT guidelines [45].

### Setting

This study will take place in a single center, located at the Croix Rousse Hospital in Lyon, France.

### Participants

#### Inclusion criteria

Volunteers for the study will be included if they are 65 years of age or older, of either sex, autonomous, able to walk ten meters alone without walking aid and able to understand instructions necessary for the correct performance of the measurements.

#### Exclusion criteria

Potential participants will be excluded from this study if they are suffering from a locomotor handicap or severe chronic progressive pathologies preventing the protocol from being carried out correctly, if they have a history of surgery, fracture or dislocation of the cervical spine, if they are institutionalized, if they have cognitive impairments (Mini Mental Statement < 20) or that their life expectancy is less than 6 months. Protected individuals: adults under curatorship or legal protection, deprived of liberty by judicial or administrative decision cannot be included.

#### Recruitment

Participants will be recruited from the local population by announcement. The study will be advertised on posters displayed at town halls, senior gyms, senior associations, pharmacies. Those who apply will be referred to a therapist who will make sure all eligibility criteria are met and give more information.

### Study schedule

#### Screening

On the day of the experiment or before, the volunteer will be welcomed by the principal investigator. After ensuring that the information provided previously has been properly understood, the investigator will present the premises and introduce the experimenters and then seek their written consent to participate in the study. An inclusion visit will also be carried out by a doctor. If they accept, the volunteer will sign the informed consent form before the study is carried out.

The participant can ask to leave the study at any time. They will be given an information sheet including the contact details of whom to approach in the event of any additional request or to report any adverse events or new facts. Finally, an SF-36 questionnaire is given to complete at home and bring back on D7.

The study design, which covers the screening, evaluation, intervention, and follow-up procedures is summarized in Fig. 1.

**Fig. 1 Fig1:**
[figure not shown]
Study schedule summary

#### Randomization and blinding

This study will use a process of allocation concealment which means that recruitment and randomization will be separated. The randomization will take place after the first session of measurements on day 0, just before the interventional part. Patients will be allocated to two groups, a sham group and an experimental group, in sequential order. Opaque envelope, prepared in advance, containing the group assignment, will be drawn by lot by the single therapist. This last will remain blind for the results obtained during evaluation and will be responsible for all the interventions in both groups. Similarly, the evaluator responsible for data collection will be blinded to the treatment allocation group (intervention or sham light touch). The placement of the hands and the timing of the techniques being strictly the same in both cases, the evaluator has no way of knowing which treatment has been applied. Subjects giving their informed consent are informed that a placebo treatment may be administered to them, and that they will not know which treatment has been applied until the end of the study. They are also told that the manipulations received are to be gentle, applied with light pressure and that they will therefore be unable to tell the difference. The subject will be questioned following the last series of measurements on their perception of the protocol received: placebo or experimental.

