#### Intervention

The experiment will take place over three measurement times on Day 0 (D0), D7 and D21. On D0 subjects will be randomized in 2 groups: experimental and placebo group. Both groups will be assessed on: SPPB, WS, lower limb strength, balance, HRV and cervical spine strength and mobility. They will also be given an SF 36 questionnaire (to complete at home and bring back to D7). Then the experimental group will receive a MFR protocol applied to the cervical spine and the placebo group will receive a placebo light touch protocol. The intervention will be followed by the same measurements as before. This schedule will be reproduced on D7. On D21, only assessment will be done. Measurements will be made by the same experimenter for all sessions for the same patient. The time of presence required is estimated at 4 h maximum: approximately 1h30 on D0 and D7 and 45 min on D21.

The MFR protocol applied to the cervical spine in this study is carried out by one therapist—Osteopath D.O. (Diploma in Osteopathy)- with one year of experience. All the gestures performed and described below are manual osteopathic techniques with myofascial aim, mastered and commonly used in osteopathic practice management. Whatever the patient's allocation group, the techniques are gentle and progressive, the patient's head (lying on his back) remaining in line with the spine.

For the treated group, initially, the manual therapist, seated at the head of the patient, will perform a “suboccipital decompression” [46]—Fig. 2a. To do this, he will position the last 4 fingers of each hand towards the lower part of the occiput, the last phalanges in contact with the sub-occipital muscles. He will look for a so-called “bone contact” on the occiput. He will apply anterior and superior continuous pressure during 15 to 20 chest breaths.

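### The treating therapist draws the allocation envelope by lot, so an assignment could be selected or redrawn, and the stated concealment does not prevent this

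*Protocol article*

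**What the plan says.** The allocation procedure is in the section Randomization and blinding of the protocol article.

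- Principle: "This study will use a process of allocation concealment which means that recruitment and randomization will be separated".
- Timing: "The randomization will take place after the first session of measurements on day 0, just before the interventional part".
- Order: "Patients will be allocated to two groups, a sham group and an experimental group, in sequential order".
- Mechanism, in the very next sentence: "Opaque envelope, prepared in advance, containing the group assignment, will be drawn by lot by the single therapist".
- Operator: "This last will remain blind for the results obtained during evaluation and will be responsible for all the interventions in both groups". The Intervention section confirms that the manual protocol "is carried out by one therapist".

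Under Screening, the principal investigator seeks consent and a doctor carries out an inclusion visit. Under Recruitment, eligibility of applicants is checked by a therapist who is not further identified. Statistical analysis and sample size gives 20 subjects per group.

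**The concern.** Two things stand out. First, adjacent sentences use two phrases for one step. If envelopes are used in a fixed order, there is nothing to draw; if they are drawn by lot, their order is not fixed. A site could not tell from the text which to follow.

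Second, and more important, the draw is made by the therapist, who necessarily knows each assignment and is about to treat the participant. With an unordered set, a drawn envelope can be returned or another one opened. Opacity hides the content of an unopened envelope, but it does not control which envelope is used. Keeping recruitment separate from randomization protects the decision to enrol, not the choice of envelope afterwards.

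With 40 participants and performance-based primary outcomes (walking speed and SPPB score), a few steered assignments could make the groups differ in ways that no analysis would reveal.

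**Working it through.** **Setting the sentences side by side**

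| Element | What the text fixes | Does it prevent selection or redrawing? |
|---|---|---|
| Separation of recruitment and randomization | Enrolment is decided before assignment | No |
| Randomization after the D0 baseline | Baseline values cannot be influenced by assignment | No |
| Therapist blind to evaluation results | No steering on measured performance | Only in part: the therapist still meets the participant and can form an impression of age or frailty |
| Opaque envelopes | Content not visible before opening | No |
| Sequential allocation | Unclear: envelopes in order, or patients in order of arrival | Only under the first reading, which the draw by lot contradicts |
| Draw by lot by the single therapist | An unordered set, operated by the person who treats | No; this is where the opening lies |

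**Number of assignments.** The plan's own figure is 20 per group. It reproduces with a one-sided test at alpha 0.05, 90% power, a difference of 0.2 m/s and the ± 0.2 read as the SD: 2 × (1.645 + 1.282)² × (0.2/0.2)² = 17.1, rounded up to 18; 18/0.9 = 20. It is used here only to set the number of envelopes at 40.

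**Predictability.** Assumption: the set holds 20 + 20 envelopes drawn without replacement. The document does not state its composition.

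- A person who tallies past assignments and guesses the arm with more envelopes left has, with n per arm, n + (2^(2n)/C(2n, n) − 1)/2 expected correct guesses.
- With n = 20: 2^40 = 1,099,511,627,776 and C(40, 20) = 137,846,528,820, ratio 7.976. So 20 + (7.976 − 1)/2 = 23.49 of 40, or 58.7%, against 20 of 40 by chance.
- Assignments known for certain before opening are those left once one arm is used up: 2n/(n + 1) = 40/21 = 1.90 of 40. A simulation of 20,000 sequences gave 1.91 certain assignments and 58.7% correct guesses.

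**Effect of small blocks on the same measure**, relevant to the fix:

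- Blocks of 4 (n = 2): 2 + (16/6 − 1)/2 = 2.83 of 4, or 70.8%.
- Blocks of 6 (n = 3): 3 + (64/20 − 1)/2 = 4.10 of 6, or 68.3%.

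Both are above the 58.7% of a single 20 + 20 order.

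**Selection or redrawing.** Nothing in the document allows its frequency or effect to be calculated.

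**The case against.** The best defence is that the sequential phrase has patients, not envelopes, as its subject. It can simply mean that participants are allocated one after another as they finish baseline, each by a drawn envelope. The two sentences then fit together, and the phrase adds no predictability. This stands: the wording is ambiguous, not a proven contradiction. It leaves the draw and its operator unchanged.

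The second defence also stands in large part. By the time of the draw the participant has consented, been seen by a doctor and been measured, so guessing the next envelope gives little scope to alter who enters. The therapist's blindness to results removes the most informative basis for steering. What remains is a chosen assignment for someone already enrolled.

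A reader might infer more than the document supports:

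- *That allocation alternates, so that every assignment after the first is known.* The text does not say so, and an envelope drawn by lot speaks against it.
- *That the therapist who checks eligibility ("Those who apply will be referred to a therapist who will make sure all eligibility criteria are met and give more information") is the one who treats.* The article does not identify that person.
- *That envelopes are unsealed or unnumbered and that no log exists.* A condensed article may leave this to the full protocol, so its silence is not evidence.
- *That envelopes are put back after use, giving a 15% chance of a 15:25 or worse split.* Nothing suggests drawing with replacement, and imbalance is not a failure of concealment.

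**Conclusion.** The point holds in a limited form. As written, the treating therapist, who cannot be blind to assignment, picks from an unordered set, and the stated form of concealment does not prevent selecting or redrawing. This rests on the mechanism and operator that the article states, not on missing detail.

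Prediction is the minor part: about 3.5 correct guesses above chance in 40 and about 1.9 certain assignments, both conditional on a 20 + 20 set drawn without replacement. Selection is the part that matters. Its size is unknown, and the safeguards around the draw reduce it without closing it. The change is worth making before any participant is randomized; the Abstract and Discussion indicate that the trial had not gone beyond inclusion or recruitment.

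**What to change.** Replace both phrases with one procedure:

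1. A person with no role in treatment or measurement generates a computer random order of 20 + 20 assignments and prepares sealed, opaque, consecutively numbered envelopes.
2. After the D0 baseline is recorded, the next envelope number is written against the participant code.
3. Only then is that envelope opened, strictly in order. The treating therapist draws nothing.

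Small blocks are not needed in a single-centre trial of this size. With one therapist who knows every assignment, they would raise guessability to about 68–71%. The single 20 + 20 order leaves predictability at about 59%; what it removes is the choice of envelope, and any departure from the order becomes visible in the record.

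The cost is a few hours of preparation and a change of wording.
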